## Schedule, interim analysis and completion of the study

The study is planned to start in summer / autumn 2014. An interim analysis will be performed in the middle of the study, ie for 66 patients. If a statistically significant difference is obtained for the primary outcome already at this stage, the study will not be continued. Otherwise, the study will continue until 133 patients have been randomized. It is estimated that it will take about five years to recruit patients. The follow-up phase will continue for another eight years.

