## Randomization

The patient is randomized 1: 1 for either elective sigmoid resection or conservative treatment. Patients are stratified based on inclusion criteria so that there are equal numbers of patients from each inclusion group in both randomization groups. Randomization is done using a computer centrally from the Helsinki University Central Hospital (HUCH). In practice, the person performing the randomisation connects to the HUCH server via the Internet, which provides the researcher with information about the patient's randomisation group. Randomization is performed at an outpatient visit, after the patient has first given written consent to participate in the study. Based on the group, treatment is selected, i.e. the patient is either placed in a surgical queue for elective sigmoid resection or given lifestyle instructions as well as instructions on how to use fiber supplementation. Upon randomization, the patient completes SF-36 and GIQLI quality of life questionnaires. Patients are analyzed according to the intention-to-treat principle according to the original randomization group.

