## The sample size

In previous publications, preoperative GIQLI has been 95-100 (SD 22) and postoperative GIQLI 112-114 (SD 19-22) (Forgione et al., 2009; Pasternak et al., 2011). The sample size calculation was made using these values, and the study aims to show a difference of 12 GIQLI points, the standard deviation being assumed to be 22 points in both groups. Using 0.05 alpha, 0.9 power, and 1: 1 allocation, a sample size per group of 60 patients is obtained. The sample size calculation was performed using G \* Power 3.1.5.1 (comparison of means, two-tailed, A priori). Approximately 10% of patients are estimated to disappear at follow-up, bringing the final sample size to a total of 133 patients.

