## Statistical analysis plan (amendment 5th Aug 2020)

Primary outcome and continuous secondary outcomes that are normally distributed will be compared using t-test and effect size will be reported as mean difference with 95% confidence interval (95%CI). Continuous secondary outcomes that were not normally distributed will be compared using Mann-Whitney U test and effect size will be reported as  $r (=Z/\sqrt{N})$  without 95%CI. Categorical secondary outcomes will be compared

using Fischer's exact test (if expected cases in one cell <5) or  $\chi^2$  test and effect size will be reported as odds ratios (OR) with 95% CIs. All outcomes will be analyzed using intention-to-treat principle where patients are analyzed in the group where they were randomized to.

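### The halfway stopping rule sets no significance threshold and the final test no reduced level; with 0.05 at both looks the overall two-sided type I error is about 8.3%, not 5%

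*Supplement*

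**What the plan says.** The section on schedule, interim analysis and completion places one interim look at 66 patients. The rule is: "If a statistically significant difference is obtained for the primary outcome already at this stage, the study will not be continued". If the result is not significant, randomisation goes on to 133. No p-value, boundary or spending function is given for the interim, and no level for the final test.

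The only significance level is in the sample size section: "Using 0.05 alpha, 0.9 power, and 1: 1 allocation, a sample size per group of 60 patients is obtained". The calculation is described there as "comparison of means, two-tailed, A priori".

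The analysis plan (amendment of 5 August 2020) states: "Primary outcome and continuous secondary outcomes that are normally distributed will be compared using t-test", with a mean difference and an ordinary 95% confidence interval. It does not mention the interim analysis, a stopping boundary, an adjusted final level or an adjusted estimate.

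**The concern.** A trial that may declare success at either of two looks has two chances of a false positive. If each look uses the full 0.05, the overall error rate exceeds 0.05. Here that affects the confirmatory test of the primary outcome, the change in GIQLI from 0 to 6 months. The background section says that no randomised comparison of surgery with conservative treatment had been published for these patients, so a false positive in either direction could carry unusual weight.

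A second matter is the estimate. A trial that stops because its interim difference is large will on average report too large a difference, and the plan provides no adjusted estimate or interval for that case.

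**Working it through.** **Inputs.** From the sample size section: two-tailed alpha 0.05, power 0.90, difference 12 points, SD 22, 60 per group, about 10% loss, 133 in total. From the schedule section: interim at 66. From the analysis plan: t-test with an unadjusted 95% interval. Assumption: both looks use two-sided 0.05.

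**The plan's own figures.**
- n per group = 2 × [(1.960 + 1.282) × 22/12]² = 70.6, so 71 (72 with the t distribution). The stated 60 is not reproduced; a one-sided calculation gives 58 to 59.
- 120/0.90 = 133.3, so 133 does follow from 60 per group.
- With 60 per group the standardised effect is 12/(22 × √(2/60)) = 2.988, and single-test power is Φ(2.988 − 1.960) = 84.8%. This shortfall from 90% is a separate matter and does not affect the type I error below.

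**Type I error as written.** The information fraction is t = 66/133 = 0.496, and the correlation of the two test statistics is √t = 0.704.

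Overall error = 1 − P(|Z1| < 1.96 and |Z2| < 1.96) = 0.0832, of which 0.050 is spent at the interim and 0.033 is added at the end.

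| Information at the interim | Overall error |
|---|---|
| 40% | 8.6% |
| 49.6% (66/133) | 8.3% |
| 55% (33 of 60 per arm) | 8.1% |
| 60% | 8.0% |

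A simulation of t-tests at 30 and then 60 per arm (200,000 runs) gave 8.4%.

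**Boundaries that hold 5%** (same formula, t = 66/133).
- O'Brien-Fleming: final z = 1.977, interim z = 1.977/0.704 = 2.81, so p = 0.0050 and 0.048. Overall 0.050.
- Haybittle-Peto: p = 0.001 and about 0.0498. Overall 0.050.

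**Power at 12 points, 60 evaluable per arm.** Single test 84.8%, O'Brien-Fleming 84.5%, unadjusted two looks 86.5%.

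**Early stopping at a true 12 points.** The plan does not say whether the 66 are randomised or evaluable, so both cases are shown. SE = 22 × √(2/m), and the chance of stopping is Φ(12/SE − z).

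| Evaluable per arm (m) | SE | Stop at p<0.05 | Stop at p<0.005 |
|---|---|---|---|
| 33 | 5.416 | Φ(2.216 − 1.960) = 60% | Φ(2.216 − 2.807) = 28% |
| 30 | 5.680 | Φ(2.113 − 1.960) = 56% | Φ(2.113 − 2.807) = 24% |

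**Mean estimate on stopping** (33 per arm) = 12 + SE × φ(a)/Φ(−a), where a = z − 12/SE.
- Unadjusted: a = −0.256, so 12 + 5.416 × 0.386/0.601 = 15.5.
- O'Brien-Fleming: a = 0.591, so 12 + 5.416 × 0.335/0.277 = 18.5.
- At a true 6 points the corresponding means are 13.5 and 17.4.

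**Average bias over all trials** (33, then 60 per arm) = P(stop) × excess on stopping × (1 − 33/60).
- Unadjusted: 0.601 × 3.48 × 0.45 = 0.9, mean 12.9.
- O'Brien-Fleming: 0.277 × 6.55 × 0.45 = 0.8, mean 12.8.

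**The case against.** **The level at each look is not written down.** This stands as a matter of wording: 0.05 at both looks is an inference. It is well supported, because 0.05 is the only level in the documents and the final interval is an ordinary 95% one. If a stricter boundary was intended, it is unrecorded, and error control then rests on something outside the plan.

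**A reader might infer that the unadjusted threshold is what exaggerates an early estimate, and that a proper boundary would cure it.** The figures do not support that. The mean estimate on stopping is larger under O'Brien-Fleming (18.5 against 15.5 at a true 12), because a stricter boundary lets only larger differences through. It makes such stops rarer, and the average bias over all trials is under one point either way. The overestimate belongs to early stopping as such and needs its own remedy.

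**A reader might infer that stopping would also end follow-up.** The text contrasts stopping with continuing randomisation to 133 and then describes eight more years of follow-up. The natural reading is that only recruitment ends. One sentence would settle it, but it is not a demonstrated fault.

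**The interim is probably past.** Recruitment was to start in 2014 and take about five years, and the analysis plan is dated August 2020. The documents do not say whether the look took place or at what threshold. This stands, and it gives the reporting remedy more weight.

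**Conclusion.** The concern holds for the type I error. As written, the plan permits two tests of the primary outcome and controls neither level beyond a single 0.05, giving about 8.3% overall, two-thirds above the nominal 5% (0.083/0.050 = 1.66). This assumes two-sided 0.05 at both looks, an interim near half the information, and a final test whenever the interim is not significant. Moving the look between 40% and 60% of the information changes the figure only from 8.6% to 8.0%. The documents do not establish that the trial was actually run at this level.

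The overestimate on early stopping is real but is not a consequence of the missing boundary. It supports asking for an adjusted estimate; it is not a further argument against the 0.05 threshold.

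**What to change.** **If the interim has not been done.** State in the protocol and analysis plan that the trial stops at the interim only if two-sided p<0.005 and that the final test is at p<0.048 (O'Brien-Fleming), or use p<0.001 and about 0.0498 (Haybittle-Peto). Dropping the interim and testing once at 0.05 is equally valid.

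**If it has been done.** Record the threshold that was actually applied. If it was stricter than 0.05, set the final level so that the two looks total 5%. If it was 0.05, report the true overall level (about 8.3% with a final test at 0.05). Tightening the final level then helps only in part, because a look at 0.05 has already spent the whole 5%: a final test at p<0.01 (final z = 2.576 in the formula above) brings the total to about 5.5%.

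**In either case.** Say whether the 66 are randomised patients or patients with 6-month GIQLI data, and that stopping ends recruitment only. If the trial stops early, report a bias-adjusted estimate and interval.

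**Cost.** A few sentences. With O'Brien-Fleming the final threshold is 0.048 instead of 0.05, power falls by about 0.3 points against a single test (84.8% to 84.5%), and the chance of stopping early at the 12-point target falls from 56–60% to about 24–28%. The sample size does not change on this account.

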## Statistical analysis plan (amendment 5th Aug 2020)

Primary outcome and continuous secondary outcomes that are normally distributed will be compared using t-test and effect size will be reported as mean difference with 95% confidence interval (95%CI). Continuous secondary outcomes that were not normally distributed will be compared using Mann-Whitney U test and effect size will be reported as  $r (=Z/\sqrt{N})$  without 95%CI. Categorical secondary outcomes will be compared

using Fischer's exact test (if expected cases in one cell <5) or  $\chi^2$  test and effect size will be reported as odds ratios (OR) with 95% CIs. All outcomes will be analyzed using intention-to-treat principle where patients are analyzed in the group where they were randomized to.

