## Outcomes

### Primary outcome

Gastrointestinal Quality of Life Index (GIQLI) - difference between 0 months and 6 months from randomisation.

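### The unadjusted t-test on the 0 to 6 month GIQLI change is valid but uses the baseline score inefficiently; baseline-adjusted regression (ANCOVA) is at least as precise and needs only a wording change

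*Supplement*

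**What the plan says.** - **Primary outcome** (Supplement, Primary outcome): "Gastrointestinal Quality of Life Index (GIQLI) - difference between 0 months and 6 months from randomisation". This is a within-patient change.
- **Test** (Supplement, Statistical analysis plan, August 2020 amendment): "Primary outcome and continuous secondary outcomes that are normally distributed will be compared using t-test and effect size will be reported as mean difference". A 95% confidence interval is to accompany it. Neither baseline GIQLI nor any other covariate is named. Non-normal continuous secondary outcomes go to a Mann-Whitney test, which takes no covariate either.
- **Baseline data** (Supplement, Randomization): "Upon randomization, the patient completes SF-36 and GIQLI quality of life questionnaires".
- **Stratification** (Supplement, Randomization): "Patients are stratified based on inclusion criteria so that there are equal numbers of patients from each inclusion group in both randomization groups". The planned test does not use this factor.
- **Secondary outcomes** (Supplement, Secondary variables): GIQLI at 12, 24, 48 and 96 months and SF-36 at 6, 12, 24, 48 and 96 months, listed as scores at each time point and not as changes.
- **Planning values** (Supplement, The sample size): "preoperative GIQLI has been 95-100 (SD 22) and postoperative GIQLI 112-114 (SD 19-22"; then "the study aims to show a difference of 12 GIQLI points, the standard deviation being assumed to be 22 points in both groups"; then "Using 0.05 alpha, 0.9 power, and 1: 1 allocation, a sample size per group of 60 patients is obtained". The calculation is described as two-tailed. The section does not say whether 22 is the SD of a score or of a change, and it gives no correlation between the two visits.

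**The concern.** A change score subtracts the whole baseline value. When the two scores correlate at less than 1 and have similar spread, that over-corrects: part of the baseline is noise that does not carry forward, and subtracting it adds variance. It also leaves the estimate exposed to chance differences in baseline between the arms. ANCOVA estimates the slope from the data and avoids both problems. The secondary GIQLI and SF-36 scores err in the other direction, since they are compared with no baseline correction although both baselines are on file.

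At stake is precision on the main question in a trial of about 120 evaluable patients. The power of the planned test also depends on a correlation that the sample-size section never states.

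**Working it through.** **1. The plan's own figure.** Inputs from the sample-size section: difference 12, SD 22, two-sided alpha 0.05, power 0.90.

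n per group = 2 × [22 × (1.960 + 1.282) / 12]² = 70.6, so 71 (72 by the exact t calculation). The stated 60 is not reproduced. At 60 per group the power is 0.848 (normal) or 0.842 (t). The dropout step does reproduce: 120 / 0.9 = 133.3, against the stated 133. This shortfall exists before any question of change score or ANCOVA arises.

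**2. General comparison.** Let S0 and S6 be the SDs at baseline and 6 months, and rho their within-group correlation.

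- Var(change) = S0² + S6² − 2·rho·S0·S6
- Var(ANCOVA residual) = S6²·(1 − rho²)
- Difference = (S0 − rho·S6)², which is never negative.

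So ANCOVA is at least as precise whatever rho is. The one qualification is the cost of estimating a slope, a variance factor of about 1 + 1/116 with 120 patients.

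**3. Equal SDs of 22 (assumption).** Here Var(change) = 2·22²·(1 − rho) and Var(ANCOVA) = 22²·(1 − rho²), so the ratio is (1 + rho)/2. Rho is not in the documents; 0.3 to 0.8 is assumed.

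| rho | SD of change | ANCOVA residual SD | Variance ratio | n per group for 90%, change / ANCOVA | Power at 60 per group, change / ANCOVA |
|---|---|---|---|---|---|
| 0.3 | 26.0 | 21.0 | 0.65 | 99 / 65 | 0.71 / 0.87 |
| 0.5 | 22.0 | 19.1 | 0.75 | 71 / 53 | 0.84 / 0.93 |
| 0.7 | 17.0 | 15.7 | 0.85 | 43 / 37 | 0.97 / 0.99 |
| 0.8 | 13.9 | 13.2 | 0.90 | 29 / 26 | 0.997 / 0.998 |

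The n columns use the normal approximation and the power columns the noncentral t. A simulation with 60 per group and 4,000 runs per rho gave variance ratios of 0.64, 0.75, 0.86 and 0.92. Both estimators centred on about 12, so neither is biased.

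With equal SDs and rho below 0.5, 2·(1 − rho) exceeds 1, so the change score is less precise than a plain comparison of 6-month scores.

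**4. Baseline SD 22, 6-month SD 19** (the lower end of the cited postoperative range). At rho 0.5: Var(change) = 484 + 361 − 418 = 427; Var(ANCOVA) = 361 × 0.75 = 270.75; ratio 0.63. Over rho 0.3 to 0.8 the ratio runs from 0.55 to 0.74, so the gain is larger than with equal SDs.

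**5. If 22 is instead the SD of the change.** At 60 per group the change-score t-test has power 0.84. ANCOVA has about 0.96, 0.93, 0.89 and 0.87 at rho 0.3, 0.5, 0.7 and 0.8.

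**6. Chance imbalance** (equal SDs of 22). The standard error of the baseline difference at 60 per group is 22 × √(2/60) = 4.0 points. An imbalance of that size moves the change-score estimate by (1 − rho) × 4.0, or 2.0 points at rho 0.5, against a target of 12. At the 66-patient interim, with 33 per group, the standard error is 22 × √(2/33) = 5.4 and the shift about 2.7 points. ANCOVA adjusts for this.

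**The case against.** The strongest reply is that nothing here is wrong. Under 1:1 randomisation the t-test on change is unbiased and matches the outcome as defined. The gain depends on a correlation that the documents do not give, and at rho 0.7 or above it is small in power terms (97% against 99%). All of that stands, and it is why this is a recommendation and not an error.

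Several stronger readings are tempting, and the documents do not support them:

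- **A reader might infer that the primary analysis throws the baseline away.** It does not. The definition "difference between 0 months and 6 months from randomisation" uses baseline by subtraction, with the slope set to 1. Only the other GIQLI and SF-36 comparisons leave it out.
- **A reader might infer that the change has SD 22 only when rho is exactly 0.5.** That needs equal SDs at both visits. With a 6-month SD of 19, the change has SD 22 at rho = 361/836 = 0.43.
- **A reader might infer that under ANCOVA the planning SD of 22 is a safe upper bound.** The residual SD stays at or below 22 only if the true 6-month SD does, and that is a planning assumption. Even at 22, 60 per group gives 84% power, so the bound would not secure the planned 90%.
- **A reader might blame the t-test for the whole gap between 84% and 90%.** At rho 0.5 with equal SDs the change has the planning SD of 22, and power is still 84%. That gap comes from the 60 per group not following from its own two-sided inputs. ANCOVA might offset it, but should not be used to cover it.

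It is also fair to say that a model with baseline alone would be incomplete, since randomisation is stratified by inclusion criterion, and that the interim test has to change along with the final one.

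**Conclusion.** The point holds as a matter of efficiency. The planned primary analysis is valid but uses baseline GIQLI with a fixed slope of 1, and the secondary questionnaire scores are compared without it. ANCOVA removes about 35%, 25%, 15% and 10% of the variance at rho 0.3, 0.5, 0.7 and 0.8 with equal SDs, and more if the 6-month SD is nearer 19. In power at 60 per group the gain is material at low to moderate correlation (16 percentage points at 0.3, about 8 to 9 at 0.5) and slight at 0.7 and above.

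The direction of the result does not depend on rho. Its size rests on an assumed rho of 0.3 to 0.8 and on reading 22 as the SD of a score, which the cited pre- and postoperative SDs suggest but the section does not state. ANCOVA also has the higher power if 22 is the SD of the change.

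**What to change.** In the statistical analysis plan:

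1. Make the primary analysis a linear regression of 6-month GIQLI on randomised group and baseline GIQLI, preferably also with the inclusion-criterion stratum used in randomisation. Report the adjusted mean difference with its 95% confidence interval.
2. Use the same model for the interim test of the primary outcome.
3. Use the same form for GIQLI at 12, 24, 48 and 96 months and for SF-36 at 6, 12, 24, 48 and 96 months, each adjusted for its own baseline.
4. Keep the t-test on change as a sensitivity analysis.
5. State in the sample-size section whether 22 is the SD of a score or of a change, and which correlation is assumed. Correct the 60 per group as a separate item.

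Items 1 to 4 cost only a dated amendment to the wording, with the interim test included. No new data, visits or patients are needed, because both questionnaires are already completed at randomisation, and the result is still a mean difference in GIQLI points. The amendment should record whether any comparison between the arms had been seen when it was made.

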### Secondary variables

1. Gastrointestinal Quality of Life Index (GIQLI) at 12 months, 24 months, 48 months and 96 months of randomisation.
2. SF-36 quality of life survey score at 6 months, 12 months, 24 months, 48 months and 96 months from randomisation.
3. Recurrence of diverticulitis and Hinchey class.
4. Undergoing emergency surgery due to diverticulosis / diverticulitis.
5. Undergoing elective sigmoid resection (conservative treatment group).
6. Complications of elective sigmoid resection.
7. Mortality (for any reason in both groups).
8. Complications of diverticulosis (fistula, stricture).
9. Stoma (permanent / temporary).

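### The planned two-group tests of GIQLI and SF-36 beyond 6 months use only patients who returned that questionnaire and ignore their earlier scores; a baseline-adjusted repeated-measures model would use the data better

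*Supplement*

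**What the plan says.** The section headed Statistical analysis plan (amendment of 5 August 2020) is the whole analysis plan. For continuous outcomes it names two methods:

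- "Primary outcome and continuous secondary outcomes that are normally distributed will be compared using t-test", reported as a mean difference with 95% confidence interval;
- "Continuous secondary outcomes that were not normally distributed will be compared using Mann-Whitney U test", reported as an effect size r without an interval.

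The primary outcome is the GIQLI "difference between 0 months and 6 months from randomisation". The Secondary variables section then lists "Gastrointestinal Quality of Life Index (GIQLI) at 12 months, 24 months, 48 months and 96 months of randomisation" and "SF-36 quality of life survey score at 6 months, 12 months, 24 months, 48 months and 96 months from randomisation". Under Randomization, both questionnaires are also completed at baseline.

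The analysis set is covered by one sentence: "All outcomes will be analyzed using intention-to-treat principle where patients are analyzed in the group where they were randomized to". No repeated-measures model, baseline adjustment, imputation, missing-data assumption or sensitivity analysis is given.

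Missing late scores are foreseen. The sample size section states that "Approximately 10% of patients are estimated to disappear at follow-up", without tying this to a visit or an arm. The schedule section states that "The follow-up phase will continue for another eight years". The Follow-up section relies on mailed questionnaires, and the Conservative treatment section ends follow-up for a patient who opts out.

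**The concern.** A patient who answers at baseline, 6, 12 and 24 months and then stops has four scores in the database and none at 48 or 96 months. The comparisons at those last two visits leave this patient out, although the earlier scores carry information on what the missing ones would have been and may be related to why the patient stopped. The intention-to-treat sentence settles the arm in which a patient is counted. It does not say how a patient without a score enters a comparison.

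The arms know their treatment, and only the conservative arm faces a decision at 6 months on whether treatment has failed. Loss that differs between the arms is therefore conceivable. If poorly scoring conservative patients stop answering more often than surgical patients do, those who remain look too well and the late benefit of resection is understated. With the reverse pattern it is overstated. At stake are the long-term quality-of-life comparisons, which are secondary outcomes.

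**Working it through.** **Inputs from the documents.** Difference 12 GIQLI points, SD 22 in both groups, 60 per group and 133 in total, loss about 10% (sample size section); scores at 0, 6, 12, 24, 48 and 96 months.

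**The plan's own loss step.** 2 × 60 / 0.90 = 133.3, which agrees with 133. (The 60 itself does not follow from the stated inputs: 2 × (1.960 + 1.282)² × 22² / 12² = 70.6, so 71 per group, or 72 with the t distribution. That is a separate matter and nothing below depends on it.)

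**Inputs assumed, because the documents do not give them.** Equal correlation between visits of 0.5 to 0.7; a true difference of 12 at every visit after baseline; patients who leave do not return; the late outcome is the score at the visit, as the secondary list reads, and not the change from baseline; total loss at 96 months of 10%, 20% or 30%; and the loss rule. Where loss depends on the score, the log-odds of leaving rise by 0.5 or 1 for each SD (22 points) by which the last observed score is lower.

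**Bias at 96 months.** Simulated with at least 200,000 patients per arm; the true difference is 12.

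| Loss rule | 10% lost | 20% lost | 30% lost |
|---|---|---|---|
| Random | 12.0–12.1 | 11.9–12.0 | 11.9–12.1 |
| Same absolute low-score rule in both arms | 11.4–11.9 | 10.9–11.8 | 10.5–11.8 |
| Only low-scoring conservative patients leave | 10.5–11.4 | 8.9–10.8 | 7.4–10.2 |

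The entries are the difference among responders, which is what the t-test estimates. An estimate using all visits (sequential regression on the full history, equivalent to a saturated repeated-measures model under this kind of loss) gave 11.9 to 12.2 under every rule.

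- At 10% loss, the last two rows give a bias of 12 − 11.9 = 0.1 to 12 − 10.5 = 1.5 points. At 30% it is 0.2 to 4.6.
- The middle row is biased because surgical patients score higher on average, so one absolute rule removes more conservative patients.
- If each arm loses its low scorers relative to its own mean in the same way, the bias is about zero.
- If the arms lose opposite kinds of patient, the bias reaches about 2 to 3 points at 10% in either direction. That is an extreme case.

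**Scale.** With 60 per arm the standard error of the difference is 22 × √(2/60) = 4.0, so 1.5 points is 1.5/4.0, or about 0.4 of a standard error.

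**Precision under random 30% loss.** Correlation 0.6, 66 randomised per arm, 1,500 runs.

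- t-test: standard error 4.57. Check: 66 × 0.7 = 46.2 responders, and 22 × √(2/46.2) = 4.58.
- Responders only, adjusted for baseline (ANCOVA): 3.68. Check: 4.58 × √(1 − 0.6²) = 3.66.
- Repeated measures: 3.59.
- Variance ratios: t-test to repeated measures (4.57/3.59)² = 1.62; t-test to ANCOVA (4.57/3.68)² = 1.54; ANCOVA to repeated measures (3.68/3.59)² = 1.05.

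Nearly all the precision gain therefore comes from baseline. For bias, ANCOVA recovers part. With only low-scoring conservative patients leaving (log-odds 1 per SD), it gives about 11.5 at 10% loss and about 10.7 at 30%.

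**The case against.** Several objections are sound and limit the point.

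- A reader might infer that a patient who misses a late visit loses all earlier data, or that the primary result is affected. Neither follows. Each score counts at the visit where it was given, and the 6-month GIQLI is the first scheduled follow-up score.
- A reader might infer that the late estimates will be biased. The documents say nothing about who will leave. Random loss, or loss with the same relative pattern in both arms, leaves the difference essentially unbiased. Conservative patients who are operated on stay in follow-up, which closes one route of selective loss.
- At the only loss rate in the documents, the bias is less than half a standard error in all but the extreme case. Baseline adjustment alone would leave about 0.5 points of it.
- The simulated loss is missing at random by construction, so a likelihood model is bound to recover 12. The simulation also ignores referral of conservative patients to resection from 6 months. That may change the late difference and weaken the link between early and late scores, so the recovery shown is not proven for this design.
- Separate testing at each visit is inferred from the named tests and the visit-by-visit outcome list. The plan does not state it outright, but it offers no other method.

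What remains is that the plan gives no way to use earlier scores when a later one is missing, and it neither states nor defends the assumption that a responders-only comparison needs. Mann-Whitney shares the weakness.

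**Conclusion.** The point holds for the secondary GIQLI scores at 12, 24, 48 and 96 months and for the SF-36 scores after 6 months. These comparisons would rest on responders alone and set aside scores already collected. The bias is possible, not shown. It is about 0.1 to 1.5 points against a true 12 at the planned 10% loss, 0.2 to 4.6 at an assumed 30%, and about zero when loss is random or follows the same relative pattern in both arms. Either direction is possible. These figures rest on the assumed correlations, loss rules and constant difference; only the 12 points, the SD of 22 and the 10% come from the documents. The loss of precision is real whatever the pattern, but most of it comes from leaving out baseline. The plan should be changed here; the 6-month primary result is not called into question by this point.

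**What to change.** In the Statistical analysis plan section, analyse GIQLI and SF-36 with one linear mixed model for repeated measures per scale:

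- include all randomised patients with any score after baseline, in the randomised arm;
- fixed effects for arm, visit, arm-by-visit, baseline score and inclusion group (the randomisation stratum), with an unstructured covariance across visits;
- report the arm difference with 95% confidence interval at 6, 12, 24, 48 and 96 months, and state in advance whether the model or the t-test is the primary analysis of the 6-month GIQLI;
- keep the t-test as a check, and Mann-Whitney for scores that are clearly not normal;
- add a sensitivity analysis for loss that is not at random, for example by shifting the unobserved late scores by a range of amounts that may differ between arms.

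The cost is plan wording and slightly more analysis work, with no new patients, visits or data. The model relies on loss being at random given the observed scores, which is an assumption but a weaker one than the responders-only t-test needs.
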